## Abstract

**Introduction:**

Antenatal maternal magnesium sulfate (MgSO_4_) administration is a proven efficacious neuroprotective treatment reducing the risk of cerebral palsy (CP) among infants born preterm. Identification of the neuroprotective component with target plasma concentrations could lead to neonatal treatment with greater efficacy and accessibility.

**Methods and analysis:**

This is a prospective observational cohort study, in three tertiary Australian centres. Participants are preterm infants, irrespective of antenatal MgSO_4_ exposure, born in 2013–2020 at 24^+0^ to 31^+6^ weeks gestation, and followed up to 2 years corrected age (CA) (to September 2023). 1595 participants are required (allowing for 17% deaths/loss to follow-up) to detect a clinically significant reduction (30% relative risk reduction) in CP when sulfate concentration at 7 days of age is 1 SD above the mean.

A blood sample is collected on day 7 of age for plasma sulfate and magnesium measurement. In a subset of participants multiple blood and urine samples are collected for pharmacokinetic studies, between days 1–28, and in a further subset mother/infant blood is screened for genetic variants of sulfate transporter genes.

The primary outcome is CP. Surviving infants are assessed for high risk of CP at 12–14 weeks CA according to Prechtl’s Method to assess General Movements. Follow-up at 2 years CA includes assessments for CP, cognitive, language and motor development, and social/behavioural difficulties.

Multivariate analyses will examine the association between day 7 plasma sulfate/magnesium concentrations with adverse neurodevelopmental outcomes. A population pharmacokinetic model for sulfate in the preterm infant will be created using non-linear mixed-effects modelling.

**Ethics and dissemination:**

The study has been approved by Mater Misericordiae Ltd Human Research Ethics Committee (HREC/14/MHS/188). Results will be disseminated in peer-reviewed journal publications, and provided to the funding bodies. Using consumer input, a summary will be prepared for participants and consumer groups.

STRENGTHS AND LIMITATIONS OF THIS STUDYThe SuPreme Study examines an entirely novel hypothesis—that the neuroprotective component of antenatal magnesium sulfate is sulfate—which has a strong scientific basis.This study is powered to detect a clinically significant reduction (30% relative risk reduction) in the proportion of infants with cerebral palsy (CP) when sulfate concentration at 7 days of age is 1 SD above the mean.An early marker of risk using the General Movements Assessment, and follow-up to 2 years corrected age ensures excellent case ascertainment of the primary outcome; CP.Multiple sulfate measurements over the first 28 days after birth in a significant subgroup of infants allows pharmacokinetic population modelling, which is critical to designing a neuroprotective sulfate supplementation trial if the hypothesis is proven.The main limitation of the SuPreme Study is the risk of loss to follow-up, with potential to reduce the study’s power.

## Introduction

More than 1 in 10 births are preterm (<37 weeks gestation),^1^ with survivors at considerable risk of life-long disabilities, including cerebral palsy (CP), intellectual impairment, social/behavioural difficulties and educational disadvantage.^2 3^ The family, health and broader societal costs are estimated at >$26 billion per annum in the USA alone.^4^

CP is a permanent condition of motor dysfunction, is the most common physical disability in childhood, and almost 50% of cases are due to preterm birth.^5^ CP has a higher disability burden than blindness, deafness, severe asthma or diabetes.^6^ Thus, any intervention that reduces the risk of CP among preterm infants, particularly a simple, low-risk, low-cost treatment, would have considerable personal and economic benefits.

Antenatal maternal magnesium sulfate (MgSO_4_) therapy is established as neuroprotective for preterm infants,^7 8^ and is now standard of care in Australia for women at risk of imminent preterm birth <30 weeks gestation.^8^ Meta-analysis of high-quality randomised controlled trials has demonstrated a 29% risk reduction in the rate of CP, and a 40% reduction in substantial gross motor dysfunction for preterm infants exposed to MgSO_4_ before birth.^7^ However, approximately 40% of mothers of preterm infants born <32 weeks gestation in Australia and New Zealand do not receive this treatment, often due to ineligibility or urgent birth.^9^ If the precise neuroprotective component of MgSO_4_ can be identified, there is potential for direct treatment of preterm newborns, with universal accessibility, to prevent neurological sequelae.

Magnesium is the putative neuroprotective component, yet there is little supportive evidence for this. Specifically, there is no evidence to suggest that magnesium deficiency or altered pharmacodynamics are present in preterm infants that antenatal MgSO_4_ could correct or overcome.^10–12^ Furthermore, studies of preterm infants have shown no association between serum Mg concentrations (at 24–48 hours of age) and motor impairment including CP^12^ and some evidence of harm from high Mg concentrations at birth which have been associated with lower locomotor scores in infancy.^13^ Maternal MgSO_4_ treatment is not without risk as there is potential for magnesium toxicity, with life-threatening cardiac and respiratory effects. Because of this, women on MgSO_4_ treatment require close monitoring,^8^ which is one of the economic limitations preventing universal use, particularly in resource-poor countries.

### Role of sulfate in fetal brain development

Sulfate is an obligate nutrient for fetal growth and development,^14–16^ and the fetus is reliant on maternally supplied sulfate via active transport across the placenta.^17^ During the embryonic period of brain development, heparan sulfate proteoglycans (HSPGs) play crucial roles in neurogenesis, cell migration, axon guidance, synaptogenesis and plasticity, with cell signalling controlled by sulfonation patterns of the heparan sulfate chains.^18 19^ Sulfate is also critical to white matter structure and function; sulfatide (cerebroside sulfate) forms a structural component of the myelin sheath, and is critical to its insulative properties.^20^ As CP arises from white matter injury, these functions are particularly pertinent.

A sulfate-specific transporter, SLC13A4, is expressed in placental syncytiotrophoblasts.^21 22^ Targeted disruption of the *Slc13a4* gene in mice leads to fetal sulfate deficiency and severe developmental phenotypes that increase in severity as gestation progresses, including perturbed vessel formation and haemorrhage.^15 23^ Similarities to adverse neurodevelopmental outcomes and vascular abnormalities (intraventricular haemorrhage (IVH), retinopathy of prematurity (ROP) and capillary haemangiomas) among preterm infants suggest a potential origin in postnatal sulfate deficiency.

SLC13A4 is also expressed in the brain where it plays an important role in supplying sulfate for the sulfonation of HSPGs in the hippocampus. Targeted disruption of *Slc13a4* gene in mice reduces sulfate supply to the brain, leading to deficits in social interaction and memory in adulthood.^24^ Importantly, administration of a source of sulfate within a defined developmental window prevented these deficits.^24^ These deficits show similarities to adverse neurodevelopmental outcomes widely recognised among preterm infants.^2^

Maternal circulating sulfate concentrations increase more than twofold in pregnancy^25 26^ due to increased sulfate reabsorption in the maternal kidneys which is mediated by increased renal expression of the *SLC13A1* gene.^21 27^ Disruption of *SLC13A1* in humans and mice causes sulfate wasting and hyposulfataemia; mutations resulting in significant loss-of-function lead to reduced fetal survival and adverse neurodevelopment of offspring.^27–30^ The hyposulfataemic impact of the loss-of-function *SLC13A1* variant N174S (allelic frequency approximately 30%) will be greater if the mother is homozygous for the variant (8% of the population), and/or if the fetus has inherited the variant.^31^

### Sulfate deficiency in the neonatal period following very preterm birth

Infants born <32 weeks gestation (very preterm (VP)/extremely preterm (EP)) will likely rapidly become deficient in sulfate due to three factors: (1) minimal dietary supply of free inorganic sulfate in breast milk (including colostrum),^32^ total parenteral nutrition solutions, and human milk fortifiers; (2) negligible capacity to generate sulfate from sulfur-containing amino acids due to low expression of cysteine dioxygenase gene^14 33^; (3) immature renal function including low expression of SLC13A1, with limited ability to reabsorb filtered sulfate.^15 21 34 35^

Maturation of various physiological systems in the preterm infant accelerates postnatally, for example, surfactant protein production^36^ and renal maturation.^35^ Hence, it is likely that preterm infants rapidly switch on expression of the cysteine dioxygenase and SLC13A1 genes after birth, and thus develop the capacity to generate and retain sulfate within days to weeks.

A pilot study at the lead study site (online supplemental file 1) demonstrated that, as predicted, sulfate concentrations among VP/EP newborns fell rapidly over the first week after birth, before stabilising and increasing thereafter. As VP/EP infants are born during a critical period of brain development, they are likely to be highly vulnerable to adverse effects of hyposulfataemia. This window of vulnerability also coincides with the occurrence of IVH and ischaemia (later manifesting as periventricular leukomalacia (PVL)), both predisposing factors for adverse neurodevelopmental outcome. The pilot study at the lead study site (online supplemental file 1) also showed that antenatal MgSO_4_ largely mitigates the occurrence of very low concentrations in the preterm infant; boosting sulfate to supra-physiological concentrations at birth which then decay to normal or adequate concentrations by which time the infant’s capacity to generate and retain sulfate may have matured. However, common reduced-function variants of renal *SLC13A1* and placental *SLC13A4* sulfate transporter genes may impede the efficacy of antenatal MgSO_4_ treatment to boost fetal sulfate concentrations.

10.1136/bmjopen-2023-076130.supp1Supplementary data

Given the strong scientific rationale for sulfate as the neuroprotective component of antenatal MgSO_4_, the aim of this study is to test the hypothesis that among VP/EP infants, severity of hyposulfataemia in the first week after birth correlates with adverse neurodevelopmental outcome. The primary outcome is CP, given the findings of the Cochrane meta-analysis of antenatal maternal MgSO_4_ treatment, but as per the recommendations of the Cochrane Review,^7^ other neurodevelopmental outcomes will be studied, including motor delay, cognitive function, language development and social/behavioural difficulties. This is particularly relevant given that animal studies suggest that sulfate deficiency has widespread effects on neurodevelopment, not confined to white matter abnormalities alone.^24 28–30 37^ Furthermore, vascular abnormalities which may be related to sulfate deficiency^15 23^ such as IVH, ROP, capillary haemangiomas will also be ascertained.

## Research hypothesis and aims

### Hypothesis

Among VP/EP preterm infants (<32 weeks gestation), plasma sulfate concentration at 7 days of age inversely correlates with adverse neurodevelopmental outcome.

### Primary aims

To determine whether there is a relationship between plasma sulfate and/or magnesium concentration in VP/EP infants at 7 days of age and formal diagnosis of CP at 2 years corrected age (CA), or absent fidgety movements^38^ at 12–14 weeks CA as a surrogate outcome when formal clinical assessment is unavailable, with subgroup analyses for EP and VP infants.To determine whether there is a relationship between plasma sulfate and/or magnesium concentration in VP/EP infants at 7 days of age and any adverse neurodevelopmental outcome at 2 years CA; motor, cognitive and language scores as assessed by Bayley Scales of Infant and Toddler Development (Bayley III/4^A&NZ^),^39 40^ behavioural difficulties as assessed by Strengths and Difficulties Questionnaire (SDQ),^41 42^ and a composite ‘any moderate-severe disability’, with subgroup analyses for EP and VP infants.To determine the optimal threshold of plasma sulfate and/or magnesium concentration identifying participants with risk of each adverse outcome; CP, motor/cognitive/language delay, behavioural difficulties, thereby identifying a potential plasma sulfate/magnesium target concentration for supplementation. Separate analyses will be performed for each adverse outcome, and for the composite ‘any moderate-severe disability’, along with separate analyses for EP and VP infants.

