## Sample size and statistical analysis

### Sample size

The study was powered for identifying the relationship between plasma sulfate and/or magnesium and the primary outcome, diagnosis of CP (primary aim 1). At the lead study site (MMH), based on audit of data, the CP rate for VP/EP survivors was 7%. The published risk reduction of antenatal MgSO_4_ on CP as per the Cochrane Review of this therapy is 29%.^7^ As such, to determine a clinically significant reduction in the proportion of infants with CP at 2 years CA (7%–5.25%, corresponding to a 30% relative reduction and an OR of 0.74 when sulfate concentration is increased by 1 SD above the mean), and assuming 80% power, a type I error of 0.05 and using plasma sulfate as a continuous predictor, 1324 infants are required. This calculation is based on using logistic regression as the primary analysis technique, and allows for a set of confounders to be included, including plasma magnesium concentration. Allowing for 17% participant loss, including deaths, withdrawals and lost to follow-up, a sample size of 1595 infants will be required.

A sample size calculation for primary aim 2 has not been performed, as the Cochrane Review^7^ was unable to demonstrate a risk reduction effect for intellectual deficits or developmental delay. Cognitive and language delay in VP infants is however much more prevalent than CP, and these outcome measures are continuous variables (standard scores). The sample size calculated for primary aim 1 will therefore be sufficient to detect a clinically significant risk reduction for cognitive/language outcomes if present. Primary aim 3 is predominantly exploratory, and as such a sample size calculation was not undertaken, and p values will not be presented.

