### Statistical methods

#### Primary aims 1 and 2

Descriptive statistics will be used to present the antenatal, intra partum, post partum, neonatal and follow-up characteristics, including plasma sulfate and magnesium concentration, of the cohort. Bivariate relationships will be explored between these characteristics and CP and adverse motor/cognitive/language/behavioural outcomes. Mixed-effects regression models will examine the association between plasma sulfate and magnesium concentrations at 7 days of age with adverse outcomes; site will be included as a random effect, with characteristics known to be associated with the outcome from literature and clinical experience, as well as demonstrating an association in bivariate analyses, included as fixed effects. The number of factors included will be restricted dependent on the prevalence of the outcome. Both unadjusted and adjusted effect estimates will be presented, along with 95% CIs, and p values for the primary model examining CP. An a priori subgroup analysis for <28 weeks versus ≥28 weeks will be undertaken.

#### Primary aim 3

Receiver operator characteristic (ROC) curves will be constructed, using CP/motor delay/cognitive delay/language delay/behavioural difficulties as individual outcomes, and the sulfate concentration as the predictor. The area under the ROC curve (AUROC) will be calculated and presented, along with the 95% CIs. The sulfate concentration that results in the best combination of sensitivity and specificity will be calculated (Youden’s index) for each outcome.

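### Magnesium is both a co-primary exposure and a confounder in the primary CP analysis, and the stated power covers sulfate only

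*Protocol article*

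**What the plan says.** The protocol article describes magnesium's place in the primary analysis in two ways.

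**As an exposure of primary interest.**
- Primary aims, aim 1: "relationship between plasma sulfate and/or magnesium concentration in VP/EP infants at 7 days of age and formal diagnosis of CP".
- Sample size, opening sentence: "The study was powered for identifying the relationship between plasma sulfate and/or magnesium and the primary outcome, diagnosis of CP (primary aim 1".
- Statistical methods, primary aims 1 and 2: mixed-effects models examine both day 7 concentrations against the outcomes. On reporting, the section says "Both unadjusted and adjusted effect estimates will be presented, along with 95% CIs, and p values for the primary model examining CP".

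**As a covariate.**
- Hypothesis: "plasma sulfate concentration at 7 days of age inversely correlates with adverse neurodevelopmental outcome". Magnesium does not appear. The end of the Introduction likewise sets out to test severity of hyposulfataemia only.
- Sample size, the calculation itself: "assuming 80% power, a type I error of 0.05 and using plasma sulfate as a continuous predictor, 1324 infants are required". The next sentence says that the calculation "allows for a set of confounders to be included, including plasma magnesium concentration".

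No sentence says which coefficient in the primary CP model decides aim 1, in what order the two ions are tested, or how the 0.05 is shared. For secondary aim 2, by contrast, the plan sets the type I error at 0.025 by Bonferroni because there are two time points.

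**The concern.** The study exists to find out which component of antenatal magnesium sulfate is neuroprotective. The Introduction sets magnesium, the usual candidate, against sulfate, the new one. A sulfate association and a magnesium association would therefore support different conclusions. Yet as aim 1 is worded, either could be offered as its answer.

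Two things are at stake:
- The Sample size section tells the reader that the study has known power to detect a magnesium relationship. If no calculation supports this, a null magnesium result could be read as more informative than it is.
- The 5% error rate belongs to one identifiable test only. With two candidate exposures and no rule, a reader of the results cannot tell which p value the 5% refers to.

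**Working it through.** **Inputs from the Sample size section.** CP rate 7%; odds ratio 0.74 per 1 SD of sulfate, taken as stated; power 80%; type I error 0.05 (sidedness not stated); predictor sulfate; n = 1324; 17% loss, giving 1595.

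**Step 1. Which test does 1324 correspond to?** For logistic regression with one standardised continuous predictor,

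n = (z₁₋α/₂ + z_power)² / [p(1 − p)(ln OR)²].

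- Denominator: 0.07 × 0.93 × (ln 0.74)² = 0.0651 × 0.09066 = 0.005902.
- Two-sided 0.05: (1.960 + 0.842)² = 7.849, and 7.849 / 0.005902 = **1330**, against 1324 stated (a difference of 0.5%).
- One-sided 0.05 gives 1047, which does not match.
- Two-sided 0.025, as a Bonferroni split over two ions would need: (2.241 + 0.842)² = 9.505, and 9.505 / 0.005902 = **1610**, which does not match.
- Loss to follow-up: 1324 / 0.83 = 1595.2, which matches 1595.

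The plan's figure is therefore a single two-sided 0.05 test of sulfate. Nothing in it is reserved for a test of magnesium. No effect size for magnesium is stated, so no power for magnesium can be derived from the section.

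**Step 2. What if either ion counted?** Suppose that both null hypotheses are true, each ion is tested at two-sided 0.05, and one significant result is enough. With independent tests the rate is 1 − 0.95² = 0.0975. For correlated tests it is 1 − P(|Z₁| < 1.96 and |Z₂| < 1.96) under a bivariate normal:

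| Absolute correlation between the test statistics (assumed) | False-positive rate |
|---|---|
| 0 | 9.75% |
| 0.3 | 9.5% |
| 0.5 | 9.1% |
| 0.8 | 7.8% |
| 0.9 | 7.0% |

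The document gives no sulfate–magnesium correlation, so the range is the result and no single row is.

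**Step 3. What would splitting alpha cost?** At 0.025 per ion the false-positive rate is at most 4.9%. The power for sulfate at n = 1324 is Φ(√(1324 × 0.0651) × 0.3011 − 2.241) = Φ(2.795 − 2.241) = Φ(0.554) = 71%, down from 80%. Restoring 80% needs 1610 evaluable infants, or 1610 / 0.83 ≈ 1940 recruited.

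**The case against.** The strongest reply is that the confirmatory contrast can already be inferred. The hypothesis is sulfate only and directional. The abstract and the strengths box describe power per SD of sulfate. The Sample size section names logistic regression as the primary technique with magnesium among the confounders. Aim 3 uses the same and/or wording, and its methods then take sulfate as the sole predictor. On this view the phrase in aim 1 is loose drafting. An aim is also not a success rule, and an observational cohort need not share alpha across separate scientific questions.

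Much of this stands, and it limits what can be claimed. Three stronger readings are tempting, and the document does not support them:

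- **That each ion is tested at 0.05, so the error rate is about 9%.** The 0.05 is stated once, for sulfate. An either-or rule is an inference from the and/or wording, and 9% also needs an assumed correlation near 0.5.
- **That a pure sulfate effect would often make magnesium look significant.** This needs magnesium to be read from a model without sulfate. The plan does not present such a model as primary, and the sample size text puts magnesium in the sulfate model.
- **That giving unadjusted beside adjusted estimates adds a further route to a positive result.** Reporting both is routine, and which one decides may be left to an analysis plan.

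The reply does not remove the conflict. The Sample size section claims power for either ion and then sizes for one, calling the other a confounder. The methods examine both ions and attach p values to the primary CP model. These are contradictory statements on the page, which is different from detail deferred elsewhere.

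**Conclusion.** The point holds as a contradiction about magnesium's role. Primary aim 1 and the opening sentence of the Sample size section make it a joint primary exposure, and the methods examine it alongside sulfate. The hypothesis leaves it out and the calculation makes it a confounder. The reproduced figure (1330 against 1324) shows that only one sulfate test was sized. The stated power for magnesium is therefore unsupported, and no alpha is reserved for it.

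The effect on error is conditional. If a significant result for either ion were taken to meet aim 1 at 0.05 each, the false-positive rate would be up to 9.75%, and between 7.0% and 9.75% for assumed correlations from 0.9 down to 0. If sulfate alone decides, the 5% stands. The document does not say which applies. This should be corrected, but it does not undermine the design.

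**What to change.** Make three places agree:

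1. **Primary aims, aim 1.** State the aim for sulfate, and list magnesium as a secondary exposure.
2. **Sample size, opening sentence.** Remove the claim of power for magnesium, so that the sentence matches the calculation below it.
3. **Statistical methods, primary aims 1 and 2.** Name one confirmatory contrast: the adjusted odds ratio for CP per 1 SD of day 7 sulfate, from the model that also contains magnesium, at two-sided 0.05. Report the magnesium coefficient from the same model as a secondary estimate with a 95% CI.

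The cost is wording only; the sample size and data collection do not change. The downside is that a magnesium association can no longer be claimed as a primary result, but the study was not sized for one. If both ions must stay primary, the plan should fix a testing order or split alpha. A Bonferroni split brings sulfate power down to about 71%, and the abstract describes a cohort born up to 2020, so further recruitment is not a realistic remedy.
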